# References

# Appendix A - Formative focus group discussion points for women (n=8-10 participants per group)

**Outline**

Group 1 - HIV-negative women presenting in ANC clinics individually – Mulago

Group 2 - HIV-negative women presenting with their partner - Mulago

Group 3 - women’s male partners – Mulago

Group 4 - HIV-negative women presenting in ANC clinics individually – Kitgum

Group 5 - HIV-negative women presenting with their partner - Kitgum

Group 6 - women’s male partners – Kitgum

Discussion focus: Primary HIV prevention for pregnant and lactating women

**Awareness of the risks**: What has the group ever heard with regards to:

- the concept of primary HIV prevention for pregnant and lactating women?
- the four pillars/prongs of prevention of mother-to-child transmission of HIV (PMTCT)?

**Understanding of the risks:**

- what puts a pregnant or lactating women at risk for HIV?
- Probe on potential increased risks for a pregnant or breastfeeding woman to become HIV-infected? Why/why not? Which are the increased risks?

What are the risks involved with:

- being an HIV-infected pregnant woman?
- being an HIV-infected breastfeeding mother?
- becoming HIV-infected while pregnant?
- becoming HIV-infected while breastfeeding?

**Beliefs:**

- What causes some women who have unprotected sex to become HIV-infected and others who also have unprotected sex to remain uninfected?
- What causes a pregnant or breastfeeding woman to become HIV-infected?
- What is the role of the men (spouses/fathers) in protecting their wives from becoming infected?
- What is the role of the men (spouses/fathers) in making their wives become infected?

**Attitudes**:

- How do doctors / midwives / traditional birth attendants help/not help pregnant or breastfeeding women protect themselves from HIV?
- How easy is it to use condoms in your couple / community? What are some barriers and facilitators to condom use? Any experiences with female condoms?

**Practices:**

- What are the cultural practices around sexual activity during pregnancy and breastfeeding? (probe about whether men leave the house / abstain / have other sexual partners)
- What are your experiences in being exposed to HIV while pregnant or breastfeeding?
- What are your experiences in protecting yourself and your baby from becoming HIV-infected while pregnant or breastfeeding?
- Please describe how easy is it to get condoms in your community?
- How many have used condoms consistently during pregnancy or breastfeeding? Please describe barriers and facilitators

**Challenges and opportunities**:

- What can a pregnant or breastfeeding woman do to avoid becoming HIV infected?
- What can a man do to help protect his pregnant or breastfeeding wife to become HIV infected?
- What services do pregnant or breastfeeding women receive to avoid becoming HIV infected? What services are missing/needed?

# Appendix B - Counseling Guide Outline

The guide will be adapted from the national HIV counseling guide and the CDC couple counseling guide and will focus on the concept of keeping the baby and family safe from HIV throughout pregnancy and breastfeeding, emphasizing the critical steps to achieve this goal, including the need to:

- check the family’s HIV status regularly
- adopt sustained preventive behaviors
- feed the baby safely and adequately
- and plan for future pregnancies

It will clarify the concepts of acute and incident infection , explain the “window” period, discuss serodiscordance and its implications and all available ways to minimize transmission risks, and will integrate the standard safe motherhood and safe infant feeding messages aimed at all pregnant and breastfeeding women.

**The guide will address six possible retesting scenarios for individual women or couples**:

1) individual woman remaining HIV-negative

2) individual woman with incident HIV infection

3) sero-concordant HIV-negative couple

4) sero-discordant couple with HIV-infected woman

5) sero-discordant couple with HIV-infected man; and

6) sero-concordant HIV-positive couple.

For each scenario, the guide will emphasize:

- primary prevention for the individual(s) remaining HIV-negative
- positive prevention for the HIV-positive individual(s)
- disclosure, communication, sex behavior, PMTCT prophylaxis and HIV care issues.

For primary prevention, the guide will address risk behaviors and sources of potential exposure to HIV since the last test, specific vulnerabilities and risks associated with different stages of the pregnancy, delivery and postpartum periods including cultural practices and beliefs associated with sexual activity during pregnancy and breastfeeding and resumption of sexual activity after delivery.

The guide will emphasize “positive living” for both positive and primary prevention (protected sex, adequate nutrition, psycho-social support, male circumcision, avoidance of unwanted pregnancies).

In the case of serodiscordance, the guide will emphasize ART for the HIV-infected couple member, and all methods recommended for pre-exposure prophylaxis at the time of the trial such as tenofovir-based pre-exposure prophylaxis and/or microbicide gel for the HIV-uninfected couple member if recommended.

A section specific to couples will incorporate this information with the guidelines currently in use in Uganda for couple HTC including establishing the conditions for couple counselling (consent, open discussion, receiving test results together, respecting the confidentiality of shared results, joint decision about disclosure to third party), the expectations from, and roles and responsibilities of each partner (respect, equal participation, responsiveness, openness, mutual support), and the particular issues related to sero-concordance and serodiscordance of results (keeping the HIV-negative partner uninfected, ongoing care and support of the HIV-positive partner, and assessing the risk of violence or abuse and strategies for avoiding it).

For couples becoming newly serodiscordant, counselors will focus on addressing the concepts, myths and misperceptions around serodiscordance and will discuss coping strategies including couple communication and mutual support. For both serodiscordant and HIV-positive seroconcordant couples, counselors will further emphasize risk reduction, PMTCT, and address reproductive health issues, including family planning for infected women.

# Appendix C - Schedule of events - WOMEN

ERHTEC = Extended Repeat HIV

Testing and Enhanced Counseling

HTC = HIV testing & counseling

STI = Sexually Transmitted Infections

**CONTROLS**

**INTERVENTION**

**- Blood draw + vaginal swab**

**- Baseline questionnaire**

**- STI TC**

**- Blood draw + vaginal swab**

**- Baseline questionnaire**

**- STI TC + Enhanced counseling**

**BASELINE**

**- Blood draw + vaginal swab**

**- Follow-up questionnaire-**

**- Repeat standard HTC**

**- Blood draw + vaginal swab**

**- Follow-up questionnaire**

**- ERHTEC HIV & STI TC**

**POST-NATAL VISITS**

**- ERHTEC (counseling only):**

**Infant feeding**

**Risk reduction**

**Family planning**

**- Blood draw + vaginal swab**

**- Follow-up questionnaire-**

**- Repeat standard HTC**

**- Blood draw + vaginal swab**

**- Follow-up questionnaire**

**- ERHTEC: HIV & STI TC**

**- Blood draw + vaginal swab**

**- Follow-up questionnaire**

**- ERHTEC: HIV & STI TC**

**- Blood draw + vaginal swab**

**- Follow-up questionnaire-**

**- Repeat standard HTC**

**- ERHTEC (counseling only):**

**Infant feeding**

**Risk reduction**

**Family planning**

**- Blood draw + vaginal swab**

**- Follow-up questionnaire**

**- ERHTEC: HIV & STI TC**

**- Blood draw + vaginal swab**

**- Follow-up questionnaire**

**- Repeat standard HTC**

**- ERHTEC (counseling only):**

**Infant feeding**

**Risk reduction**

**Family planning**

**- Blood draw + vaginal swab**

**- Follow-up questionnaire**

**- ERHTEC: HIV & STI TC**

**- Follow-up questionnaire**

**- Blood draw + vaginal swab**

**- Repeat standard HTC**

**- ERHTEC (counseling only):**

**Infant feeding**

**Risk reduction**

**Family planning counseling**

**Final Assessment (24 mos or end of BF)**

**- Blood draw + vaginal swab**

**- Final questionnaire**

**- ERHTEC: HIV & STI TC**

**- Blood draw + vaginal swab**

**- Final questionnaire**

**- ERHTEC: HIV + STI TC**

**** The timing and events of the late pregnancy and 6-week visits will depend of the gestational age of the woman at enrolment (see Protocol C.5.1)

***Appendix C (continued)* – Schedule of events - MEN**

ERHTEC = Extended Repeat HIV

Testing and Enhanced Counseling

HTC = HIV testing & counseling

STI = Sexually Transmitted Infections

**CONTROLS**

**INTERVENTION**

**- Blood draw + urethral swab**

**- Baseline questionnaire**

**- STI TC**

**- Blood draw + urethral swab**

**- Baseline questionnaire**

**- STI TC + Enhanced counseling**

**BASELINE**

**- Blood draw + urethral swab***

**- Follow-up questionnaire**

**- Repeat standard HTC**

**- Blood draw + urethral swab**

**- Follow-up questionnaire**

**- ERHTEC: HIV & STI TC**

**POST-NATAL VISITS**

**- ERHTEC (counseling only):**

**Infant feeding**

**Risk reduction**

**Family planning**

**- Blood draw + urethral swab***

**- Follow-up questionnaire**

**- Repeat standard HTC**

**- Blood draw + urethral swab**

**- Follow-up questionnaire**

**- ERHTEC: HIV & STI TC**

**- Blood draw + urethral swab***

**- Follow-up questionnaire**

**- Repeat standard HTC**

**- Blood draw + urethral swab**

**- Follow-up questionnaire**

**- ERHTEC: HIV & STI TC**

**- ERHTEC (counseling only):**

**Infant feeding**

**Risk reduction**

**Family planning counseling**

**- Blood draw + urethral swab**

**- Follow-up questionnaire**

**- ERHTEC: HIV & STI TC**

**- Blood draw + urethral swab***

**- Follow-up questionnaire**

**- Repeat standard HTC**

**- ERHTEC (counseling only):**

**Infant feeding**

**Risk reduction**

**Family planning counseling**

**- Blood draw + urethral swab**

**- Follow-up questionnaire**

**- ERHTEC: HIV & STI TC**

**- Blood draw + urethral swab***

**- Follow-up questionnaire**

**- Repeat standard HTC**

**- ERHTEC (counseling only):**

**Infant feeding**

**Risk reduction**

**Family planning counseling**

**cotra**

**Final Assessment (24 mos or end of BF)**

**- Blood draw + urethral swab**

**- Final questionnaire**

**- ERHTEC: HIV & STI TC**

**- Blood draw + urethral swab**

**- Final questionnaire**

**- ERHTEC: HIV + STI TC**

**** The timing and events of the late pregnancy and 6-week visits will depend of the gestational age of the woman at enrolment (see Protocol C.5.1)

* Urine or swab for STI testing to be collected only from symptomatic men at these visits

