## C.5 Follow-up

### C.5.1 Repeat HTC in late pregnancy (>36 weeks)

All women will be given an appointment to be retested and counseled for HIV in late pregnancy as per WHO and Uganda MOH recommendations. Women enrolled at or before the 16th gestational week will be given an appointment for ERHTEC or repeat HTC at 28 weeks of gestation. Women enrolled after the 16th up to the 32nd gestational week will be given an appointment for ERHTEC or repeat HTC at 36 weeks of gestation, or at the first signs of labor, whichever comes first. Women enrolled between the 32nd and 36th gestational week will be given an appointment for ERHTEC or repeat HTC 6 weeks later or at the first signs of labor, whichever comes first. Women enrolled after the 36th gestational week will be given an appointment for repeat HTC at the 6-week post-partum visit to coincide with the first routine immunization visit. In the event that a pregnant woman or couple does not return on the scheduled appointment but presents for delivery, she/they will be retested immediately before or after delivery as per the WHO recommendation. At the late pregnancy retesting visit, all women and men randomized to the intervention arms (Individual and Couple Arms ‘2’) will receive the ERHTEC intervention while women and men randomized to the control arms (Individual and Couple Arms ‘1’) will receive standard HIV retesting and counseling. In addition, both intervention and control women will be bled for syphilis testing and hemoglobin measurement and a vaginal swab will be collected for testing for Gonorrhea/ Chlamydia (G/C), Trichomonas vaginalis (Tv) and the presence of semen (Y chromosome). Symptomatic men will be bled for syphilis testing and asked for a urine sample or urethral swab for G/C and Tv testing. All enrolled women and couples will be asked to answer a follow-up behavioral questionnaire about their sexual and relational behaviors, and reproductive intentions, including family planning. All interviews will be conducted in the language of the participants.

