**C.5.2 Postpartum intervention schedule and assessments**

After the late pregnancy visit, all women and couples in the intervention arm will be asked to return at 6 weeks and 3 months postpartum and every 3 months thereafter until the end of follow-up at 24 months postpartum or 6 weeks after the end of breastfeeding, whichever occurs first. Women and couples in the control arm will be asked to return at 3 and 6 months postpartum and every 6 months thereafter until the end of follow-up at 24 months postpartum or 6 weeks after the end of breastfeeding, whichever occurs first.

Participants randomized to the intervention arms (Arms I-2 & C-2) will receive enhanced counseling at every visit and will be retested for HIV at 3, 6, 12, 18 and 24 months postpartum (or at the end of follow-up, whichever occurs first). At these visits, both intervention and control women and men participants will undergo a physical examination and will be asked to answer individually a follow-up behavioral questionnaire about their sexual behaviors, relational and reproductive intentions, including family planning. At these same visits, all women will be bled for syphilis and HIV rapid testing and two vaginal swabs will be collected, one for G/C, and Tv testing and the other for Y chromosome detection while a blood or urine sample or urethral swab will be obtained from symptomatic men for syphilis, G/C and Tv testing [*See Schedule of Events, Appendix C*].

At the end of follow-up, all study participants irrespective of their arm assignment will undergo a physical examination, will be asked to answer individually an end-of-study questionnaire and will be bled for syphilis and HIV rapid testing and a vaginal or urethral swab will be collected for G/C and Tv testing. A vaginal swab will also be collected from women to test for the presence of Y chromosomes.

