**C.7 Measures**

**C.7.1 Primary outcomes**

The primary outcomes are the frequency of unprotected sex and the incidences of HIV and STI over follow-up. The trial is powered to detect a 10% difference in the frequency of unprotected sex[[2]](#footnote-3) accounting for a 50% loss to follow-up over 2 years. The frequency of unprotected sex will be determined as the self-reported number of episodes of unprotected vaginal intercourse with inconsistent or no condom use in the last 3 months and will be validated by Y chromosome detection in vaginal swabs. Reports by each partner in the couple trial will be treated as two correlated outcomes.

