In calculating STI incidence, time-at-risk will be censored for 14 days following initiation of each STI treatment. Treatment effects on incident STIs will be assessed using logistic models, with robust standard errors to account for clustering within women and couples, and inverse weighting to account for informative dropout. HIV incidence will be modeled using pooled logistic models for internal-censored failures, again with robust standard errors and inverse weighting

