***Appendix C (cont’d*) - Summary of events and measurements by study arms and visits**

|  | **Controls** | | **All** | | | **Intervention arm (ERHTEC)** | | |
| --- | --- | --- | --- | --- | --- | --- | --- | --- |
| **Follow-up** | **Standard counseling** | **Standard HIV testing & counseling** | **STI testing** | **Behavioral questionnaire, blood draws + vaginal/urethral swabs** | **Qualitative intervention assessment** | **HIV testing & enhanced counseling** | | **Risk reduction counseling,**  **Infant feeding/nutrition education & Family planning counseling** |
| Formative |  |  |  |  | **X** |  | |  |
| Baseline | **X** | **X** | **X** | **X** |  | **X** | | **X** |
| Late pregnancy | **X** | **X** | **X*** | **X** |  | **X** | | **X** |
| *6 weeks* | ***x*** |  |  |  |  |  | | ***X*** |
| 3 months | **X** | **X** | **X*** | **X** |  | **X** | | **X** |
| 6 months | **X** | **X** | **X*** | **X** |  | **X** | | **X** |
| *9 months* |  |  |  |  |  |  | | ***X*** |
| 12 months | **X** | **X** | **X*** | **X** | **X** | **X** | | **X** |
| *15 months* |  |  |  |  |  |  | | ***X*** |
| 18 months | **X** | **X** | **X*** | **X** |  | **X** | | **X** |
| *21 months* |  |  |  |  |  |  | | ***X*** |
| 24 months**+** | **X** | **X** | **X** | **X** | **X** | **X** | | **X** |
|  |  | **Measurements** | | | | |  | |

 **Retention visits:
-** Participants in the intervention arms will receive enhanced counseling but blood and vaginal swabs or urine samples will not be
 collected unless deemed necessary by the clinician.
- Participants in the control arms will receive standard counseling when study visits correspond to scheduled post-natal visits but
 will not be asked to come back otherwise until their final follow-up visit.
- No questionnaire will be administered during retention visits.

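### The protocol contradicts itself on whether interim STI testing of men is restricted to symptomatic men in both arms or only in the control arm, and C.8.2 does not confine the STI comparison to specimens common to both arms.

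*Protocol*

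**What the plan says.** C.7.1 makes STI incidence primary: "The primary outcomes are the frequency of unprotected sex and the incidences of HIV and STI over follow-up".

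**Men, body text.** For the late-pregnancy visit C.5.1 says "Symptomatic men will be bled for syphilis testing and asked for a urine sample or urethral swab for G/C and Tv testing". For the postpartum visits C.5.2 describes procedures for both arms together and adds "while a blood or urine sample or urethral swab will be obtained from symptomatic men for syphilis, G/C and Tv testing". Neither section separates the arms. In the Appendix C summary table, STI testing sits in the block headed for all participants, and a footnote limits it to symptomatic men at the interim time points.

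**Men, flow chart.** In the men's schedule of events, the interim control boxes (those with standard repeat HTC) list "Blood draw + urethral swab" with an asterisk, explained as "Urine or swab for STI testing to be collected only from symptomatic men at these visits". The interim intervention boxes (those labelled "ERHTEC: HIV & STI TC") list the same procedure without the asterisk.

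**Retention visits.** The note under the summary table says that, for participants in the intervention arms, samples at the retention visits (6 weeks, 9, 15 and 21 months) are not "collected unless deemed necessary by the clinician". Control participants have no matching provision and are not called back apart from routine post-natal visits. C.5.2 agrees on the visit pattern: quarterly for intervention, and 3, 6 and then every 6 months for control. C.5.4 says instead that everyone is on a quarterly schedule.

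**Analysis.** C.8.2 says "Treatment effects on incident STIs will be assessed using logistic models, with robust standard errors to account for clustering within women and couples". It does not say whose infections, or which specimens, count.

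**The concern.** A comparison of STI incidence is interpretable only if both arms are looked at equally hard. The men's chart, taken as printed, samples all intervention men at five interim visits but only symptomatic control men. Infections without symptoms would then be found in one arm and missed in the other. The discretionary clause at retention visits adds a smaller opening of the same kind, for women and men, again only in the intervention arms.

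Both routes put more detected infections in the intervention arm and so work against ERHTEC. There is also a path in the other direction. Under C.5.5, partners of infected participants are notified and treated when possible, so more testing of intervention men could lower what their partners' later swabs show. If sites work from the chart, neither effect can be undone after data collection.

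**Working it through.** The protocol gives no figure for STI testing by arm, so there is none to reproduce. Its 80% power statement concerns unprotected sex and does not bear on this point.

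**Step 1: the interim boxes in the men's chart.** The chart's layout was lost in the text available for review, so boxes are assigned to arms by their labels.

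| Visit | Control box marked symptomatic-only | Intervention box marked symptomatic-only |
|---|---|---|
| Late pregnancy | yes | no |
| 3 months | yes | no |
| 6 months | yes | no |
| 12 months | yes | no |
| 18 months | yes | no |
| Total | 5 of 5 | 0 of 5 |

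At baseline and at the final visit, all men are sampled in both arms.

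**Step 2: the other places.** C.5.1 (late pregnancy), C.5.2 (postpartum) and the summary table with its footnote all restrict interim testing of men to those with symptoms, with no arm distinction. Three places therefore conflict with one chart.

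**Step 3: women.** Scheduled swabs are taken at the same visits in both arms: late pregnancy, 3, 6, 12, 18 and 24 months or end of follow-up.

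**Step 4: size if the chart were followed and men's infections were counted.**

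Inputs from the protocol: 6 follow-up assessments (5 interim and 1 final). Per arm there are 205 women enrolled alone and 205 couples, so 410 women and 205 men.

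Assumptions:
- true incidence is equal in the two arms, and equal per test interval in women and men;
- there is no attrition;
- an infection missed at one visit does not persist to the next test;
- the mark covers every STI test;
- a share s of men's infections is symptomatic, with s from 0.3 to 0.5. The protocol gives no value.

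Men only. Detections per man are proportional to 6 in the intervention arm and 5s + 1 in the control arm:

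ratio = 6 / (5s + 1)

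- s = 0.5: 6 / 3.5 = 1.71
- s = 0.3: 6 / 2.5 = 2.40

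Pooled with women:

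ratio = (410 × 6 + 205 × 6) / (410 × 6 + 205 × (5s + 1))

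- s = 0.5: 3,690 / (2,460 + 717.5) = 3,690 / 3,177.5 = 1.16
- s = 0.3: 3,690 / (2,460 + 512.5) = 3,690 / 2,972.5 = 1.24

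Over a wider range, s = 0.1 gives 4.00 in men and 1.33 pooled, and s = 0.9 gives 1.09 and 1.03. Under the arm-neutral rule both ratios are 1.00.

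**Step 5: retention visits.** Intervention participants have up to 4 extra visits at which sampling is allowed. No rate of clinician-ordered sampling is given, so the effect cannot be put in figures.

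**The case against.** The strongest reply is that unequal testing of men is not the plan. Three places set one rule for both arms, the chart's footnote names no arm, and the likeliest explanation is asterisks left off one column. That stands. A reader of the chart alone might infer that the protocol has chosen to test the arms differently; the document as a whole does not support that.

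Other stronger readings also fail:

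- A reader might infer that the retention visits are extra sampling visits for intervention women. The note speaks of participants, so men are included, and sampling is the exception.
- A reader might infer from the couple clustering in C.8.2 that men's infections are counted. It suggests this but does not state it. C.8.2 names male partners explicitly for the sex-episode counts and not for STIs, and Aims 1 and 2 name women only.
- A reader might take 1/s, or 2.0 to 3.3, as the distortion in men. That covers only the five interim visits and leaves out the final visit, where all men are tested.
- Taken literally, the footnote limits only urine and swabs. The blood draw stays in both arms' boxes, so syphilis testing might not differ and the ratios above would be too high.

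It can also be said that STI testing appears inside the ERHTEC boxes, so treatment after extra detection is part of the intervention; that the trial is powered on unprotected sex and not on STIs; and that the endpoint population may be left to the SAP. The first is arguable, but it does not help where the body text gives both arms the same testing rule. The second lowers the stakes without removing a primary outcome. The third would hold if the schedule were symmetric. Here the protocol's own visit schedule creates specimens in one arm that have no counterpart in the other.

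**Conclusion.** The point holds as an internal contradiction with consequences for a primary outcome. The men's chart conflicts with C.5.1, C.5.2 and the summary table on interim STI testing. C.5.4 conflicts with C.5.2 and the retention-visit note on whether control participants are seen quarterly. C.8.2 does not limit STI events to specimens that both arms provide.

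If sites followed the chart and men's infections were counted, the spurious ratio against ERHTEC would be about 1.7 to 2.4 in men and 1.16 to 1.24 pooled, on the assumptions listed in the working. If sites followed the body text, the testing rule for men would add no distortion. Women's scheduled testing is balanced on either reading. What remains for women is the discretionary sampling, of unknown size, and, if the chart is followed, any treatment prompted by extra testing of their partners.

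**What to change.** 1. Reconcile the men's schedule of events with C.5.1, C.5.2 and the summary table, so that one testing rule for men is printed for both arms everywhere.
2. Reconcile C.5.4 with C.5.2 and the retention-visit note on whether control participants attend between the common visits.
3. In C.8.2, define the main STI comparison on protocol-scheduled specimens from women at the visits common to both arms (late pregnancy, 3, 6, 12, 18 and 24 months or end of follow-up), in line with Aims 1 and 2.
4. Report infections in men, and infections found on unscheduled or retention-visit samples, separately by arm and outside the main comparison.

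The cost is a corrected chart and a few sentences of wording, with no added visits or tests. A few events leave the main STI comparison. A women-only endpoint does not by itself remove any effect of unequal partner testing and treatment, so item 1 is needed as well as item 3.
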